## Abstract

**Introduction: **Patient-derived xenografts (PDX) can be used to explore tumour pathophysiology and could be useful to better understand therapeutic response in breast cancer. PDX from mammary tumours are usually made from metastatic tumours. Thus, PDX from primary mammary tumours or after neoadjuvant treatment are still rare. This study aims to assess the feasibility to establish xenografts from tumour samples of patients with triple negative or luminal B breast cancer in neoadjuvant, adjuvant or metastatic setting.

**Methods: **XENOBREAST is a single-centre and prospective study. This feasibility pilot trial aims to produce xenografts from tumour samples of patients with triple negative or luminal B breast cancer. Patient enrolment is expected to take 3 years: 85 patients will be enrolled and followed for 28 months. Additional blood samples will be taken as part of the study. Surgical specimens from post-NAC surgery, primary surgery or surgical excision of the metastases will be collected to establish PDX. Histomolecular characteristics of the established PDX will be investigated and compared with the initial histomolecular profile of the collected tumours to ensure that they are well-established.

**Ethics and dissemination: **XENOBREAST belongs to category 2 interventional research on the human person. This study has been approved by the Sud Méditerranée IV – Montpellier ethics committee. It is conducted notably in accordance with the Declaration of Helsinki and General Data Protection Regulation (GDPR). Study data and findings will be published in peer-reviewed medical journals. We also plan to present the study and all data at national congresses and conferences.

**Registration:** ClinicalTrials.gov ID
NCT04133077; registered on October 21, 2019.

## Introduction

Breast cancer can be classified into different molecular subtypes according to gene expression: luminal A (Hormone Receptor positive (HR+)/human epidermal growth factor receptor 2 negative (HER2-), with high HR expression and low levels of the protein Ki-67), luminal B (HR+ either HER2+ or HER2- with high levels of Ki-67 and with low HR expression), HER2-enriched (amplification of
*ERBB2* gene, regardless of HR status) and triple-negative (HR-/HER2-). Luminal B and triple-negative tumours account respectively for approximately 20% and 10–15% of all breast cancers
^
1–
3
^. Although rarer than luminal A breast cancers, luminal B and triple-negative tumours are often high-grade tumours with a poorer prognosis
^
1
^.

The establishment of patient derived xenografts (PDX) could be useful to discover new treatments and strategies needed in the fight against these subtypes of breast cancer. PDX are derived from tumour tissue in which the tumour architecture and the proportion of cancer and stromal cells are both maintained: advantages not found in cell lines. Therefore, PDX effectively model intra- and inter-tumoural heterogeneity
^
4,
5
^. It is important to note that PDXs have been shown to undergo mouse-specific tumour evolution
^
6
^.

Thus, PDX are used to answer questions such as the contribution of tumour heterogeneity to therapeutic response, patterns of tumour progression during metastatic progression and mechanisms of treatment resistance
^
7,
8
^.

Most of the available PDX or organoids, which have been xenografted into mice and recapitulate the primary tumours, are generated from primary breast cancer tissue
^
5,
9–
11
^. In contrast, generated PDX from metastatic tumours remain rarer and may allow the identification of eventual molecular therapeutic targets in metastatic setting.

It is also necessary to have PDX models from primary breast lesions that are resistant to neoadjuvant therapies. Recent prospective studies show that PDX can be obtained from neoadjuvant breast tumours and demonstrate the feasibility of tumour sequencing in these situations
^
12,
13
^. Breast cancer patients with residual disease after neoadjuvant chemotherapy (NAC) have an increased risk of recurrence. Similarly, high-grade breast tumours treated by primary surgery are very rare, poorly known, and aggressive.

The production of PDX from post-NAC residual breast tumours or from high-grade breast tumours will provide data on the molecular characteristics of these tumours with a high risk of recurrence.

In this study, we want to establish PDX from tumour samples of patients with triple-negative and luminal B breast cancers in neoadjuvant, adjuvant or metastatic settings. In addition, to verify whether or not the PDX obtained is consistent with the original tumour, we will study the tumour exomes of both the PDX and the original tumour. The study of the patients’ constitutional exome will serve as the basis for this comparison and is an essential element in the overall somatic analysis.

## Methods

### Study design

This is a single-centre prospective trial designed to establish xenografts from surgical specimens of patients with triple negative or luminal B breast cancer in neoadjuvant, adjuvant or metastatic setting. Patient enrolment is expected to take 3 years: 85 patients will be enrolled and followed during 28 months.

Study design is presented in
Figure 1. The management of patients in the study may vary depending on the setting: neo-adjuvant, adjuvant or metastatic. In all the settings and as a part of their medical follow-up, patients will go through a pre-operative biological assessment. For patients in metastatic setting, this assessment will be performed before surgical excision of the metastases. Blood samples will be used to perform sequencing of the patient's constitutional exome. At the end of the surgery, one sample of the surgical specimen will be taken to generate PDX and another one to sequence the patient's tumour exome.

**Figure 1. f1:**
[figure not shown]
Design of the XENOBREAST study. Adult women with triple negative or luminal B breast cancer in neoadjuvant, adjuvant or metastatic setting will be included. In all the settings, patients will go through a pre-operative biological assessment. Blood samples will be used to perform sequencing of the patient's constitutional exome. At the end of the surgery (post-NAC surgery, primary surgery or surgical excision of the metastases), a sample of the surgical specimen will be taken to generate patient-derived xenografts (PDX) and another one to sequence the patient's tumour exome.

Participants can withdraw at any time. Data obtained will be retained with consent, and any reasons given for withdrawal will be recorded.

### PDX generation

The patient-derived tumour xenograft platform called XenTech will generate the PDX. All PDX will be established as approved by the ethical authorisation #16569: « Développement d’une collection de modèles de tumeurs humaines greffés sur souris (PDX) ». The different steps of the development of an established xenograft model are summarized in
Figure 2. Overall, fresh surgical tissue will be cut into small fragments and grafted into the inter-scapular region or into the renal capsule of 6- to 13-week-old female immunodeficient or severe-combined immuno-deficiency (SCID) or non-obese diabetic SCID mice. The inter-scapular site allows easy access to a well vascularized region with tissue that in female mice is in continuity with the mammary gland. Although the use of extracellular matrix tends to increase xenograft take rates, tumor fragments will be implanted without any matrix. Mice should weigh 18g at 6 months. At the onset of tumour growth, a latency period of 1 to 9 months is expected. The mouse generation with the patient derived graft will be called F0 and the following generations will be numbered F1, F2, and F3. When the tumour volume reaches the ethical limit (10% of the total weight of the mouse), the tumour is removed and fragmented as follows: a part is grafted to a new set of mice; a second part is fixed in formalin and embedded in paraffin for histological studies; a third part is frozen in liquid nitrogen for molecular studies; and a last part is frozen in a 10% DMSO solution to generate a viable tissue stock. These steps are repeated for the F1, F2 and F3 generation. A xenograft will be considered as well-established in the third generation (F3). When it is necessary, the animal will be sacrificed by cervical dislocation. For the duration of the study, mice will be housed, by a maximum of 6, in individually ventilated cages. They will be housed in a light-dark cycle with temperature and hygrometry control. The mice will have throughout the duration of the project a complete diet and drinking water. For the ER+ PDX models, mice will receive 17β-estradiol supplementation in the drinking water, useful for the establishment of these models
^
14
^. No estrogen pellets will be implanted.

**Figure 2. f2:**
[figure not shown]
Scheme summarizing the different steps from the patient's surgery to the generation of an established patient-derived xenografts (PDX) model. Fresh surgical tissue will be grafted into the inter-scapular region or into the renal capsule of immunodeficient or severe-combined immuno-deficiency mice. When the tumour volume reaches the ethical limit, the tumour is removed and fragmented as follows: a part is grafted to a new set of mice; a second part is fixed in formalin and embedded in paraffin for histological studies; a third part is frozen in liquid nitrogen for molecular studies; and a last part is frozen in a 10% DMSO solution to generate a viable tissue stock. These steps are repeated for the F1, F2 and F3 generation. A xenograft will be considered as well-established in the third generation (F3).

### Sample selection

Inclusion and exclusion criteria are presented in
Table 1. Briefly, adult women (18 years or older) with triple-negative or luminal B breast cancer in neoadjuvant, adjuvant or metastatic setting will be included.

**Table 1. T1:** Inclusion and exclusion criteria.

Inclusion criteria	• Female • Age ≥ 18 years • ECOG (Eastern Cooperative Oncology Group) performance status ≤ 2 • Women with : ○ high grade metaplastic triple-negative (TN) breast cancer, histologically proven before treatment, receiving neoadjuvant chemotherapy and having, after treatment, a breast residue of at least 15 mm on the specimen. The mammary residue will measure at least 15 mm on the mammography performed at the end of neoadjuvant treatment OR ○ high grade metaplastic triple-negative (TN) breast cancer, histologically proven before treatment, treated by primary surgery with a tumour size of at least 15 mm on the specimen OR ○ inflammatory TN breast cancer (T4d), histologically proven prior to treatment, receiving neoadjuvant chemotherapy and having, after treatment, a breast residue of at least 15 mm on the specimen. The mammary residue will measure at least 15 mm on the mammography performed at the end of the neoadjuvant treatment OR ○ TN breast cancer other than non-metaplastic or inflammatory, histologically proven prior to treatment, receiving neoadjuvant chemotherapy and having, after treatment, a mammary residue of at least 30 mm on the specimen. The mammary residue will measure at least 15 mm on the mammography performed at the end of the neoadjuvant treatment OR ○ Luminal B breast cancer, histologically proven prior to treatment, receiving neoadjuvant chemotherapy and having, after treatment, a mammary residue of at least 30 mm on the specimen. The mammary residue will measure at least 15 mm on the mammography performed at the end of the neoadjuvant treatment OR ○ Metastatic TN or luminal B breast cancer, histologically proven at diagnosis, with an operable metastasis and having after chemotherapy a residue of at least 10 mm on the surgical specimen. Residual metastasis will measure at least 15 mm on imaging. • Patients in a metastatic situation can be included regardless of the therapeutic line • Affiliation to social security • Signature of the participation consent of the study
Exclusion criteria	• Pregnant woman • Patient deprived of liberty by court or administration decision • In neoadjuvant situation: neoadjuvant treatment by radiotherapy or hormone therapy • Refusal to participate to the study

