### Sample size calculation

This feasibility study aims to obtain xenografts from tumours that are either rare or tumours that are resistant to treatment and therefore difficult to establish. We consider that a minimum of five successful grafts would meet this objective. Under these conditions, knowing the graft success rate specific to each histological type and the proportion of luminal B (2/3) and triple-negative breast cancers (1/3), we calculate the number of subjects required so that the lower bound of the 95% confidence interval (CI) of the success rate multiplied by the number of subjects is ≥5.

To obtain a xenograft, the average rate is 30% from triple-negative tumours and 10% from luminal B tumours. Taking these data into account, we will include 2/3 luminal B tumours and 1/3 triple negative tumours: the expected rate of successful xenografts will be approximately 17%. The number of patients needed to be included is therefore at least 65: lower bound of the CI-95% of 17% for 65 subjects = 8% or 5 patients (8%×65=5.2).

Since for some patients the tumour will be of sufficient size for imaging, but of insufficient size in the operating room, we consider that this number should be increased by 30%, to a total number of 85 patients.

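### As worded, the fourth inclusion criterion leaves ordinary triple-negative cancer after neoadjuvant chemotherapy with no non-metastatic route into the trial

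*Protocol article*

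**What the plan says.** Table 1 of the protocol article (Sample selection) lists six disease criteria joined by OR. Four concern non-metastatic TN disease:

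- **Criterion 1:** "high grade metaplastic triple-negative (TN) breast cancer, histologically proven before treatment, receiving neoadjuvant chemotherapy", with "a breast residue of at least 15 mm on the specimen".
- **Criterion 2:** the same high grade metaplastic TN, but "treated by primary surgery with a tumour size of at least 15 mm on the specimen".
- **Criterion 3:** "inflammatory TN breast cancer (T4d), histologically proven prior to treatment, receiving neoadjuvant chemotherapy", with the same 15 mm specimen requirement as criterion 1.
- **Criterion 4:** "TN breast cancer other than non-metaplastic or inflammatory, histologically proven prior to treatment, receiving neoadjuvant chemotherapy", with "a mammary residue of at least 30 mm on the specimen".

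Criterion 5 is luminal B after neoadjuvant chemotherapy. Criterion 6 is metastatic TN or luminal B disease with an operable metastasis, with no restriction on histology.

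The sentence introducing the table summarises the population as adult women with TN or luminal B cancer in any of the three settings. The Sample size calculation section states the planned mix: "we will include 2/3 luminal B tumours and 1/3 triple negative tumours".

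**The concern.** Criterion 4 should pick up the TN patients left over once metaplastic and inflammatory tumours have been dealt with. With the prefix 'non-' in place it points back at metaplastic tumours, and the remaining group is not described anywhere in the non-metastatic part of the list.

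This is an eligibility rule. Someone applying the text turns away a group that the trial evidently wants. Someone applying the evident intent enrols patients who do not meet the criterion as written. Either way, the tumours that enter the denominator of the success percentage (Statistical analysis, primary analysis) are not those the written criterion defines together with its introduction.

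**Working it through.** This is a matter of wording and logic, so the check lists every type of non-metastatic TN tumour after neoadjuvant chemotherapy against the criteria that could admit it.

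**1. Two ways to parse criterion 4.**
- Strict: NOT (non-metaplastic OR inflammatory) = metaplastic AND not inflammatory.
- Loose: (NOT non-metaplastic) OR inflammatory = metaplastic OR inflammatory.

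**2. Enumeration.** Criterion 2 is left out because it concerns primary surgery, and criterion 6 because it requires a metastasis. The last column reads criterion 4 as other than metaplastic or inflammatory.

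| Metaplastic | High grade | Inflammatory | Crit. 1 (15 mm) | Crit. 3 (15 mm) | Crit. 4 strict (30 mm) | Crit. 4 loose (30 mm) | Crit. 4 corrected (30 mm) |
|---|---|---|---|---|---|---|---|
| no | no | no | no | no | no | no | **yes** |
| no | yes | no | no | no | no | no | **yes** |
| no | no | yes | no | yes | no | yes | no |
| no | yes | yes | no | yes | no | yes | no |
| yes | no | no | no | no | yes | yes | no |
| yes | yes | no | yes | no | yes | yes | no |
| yes | no | yes | no | yes | no | yes | no |
| yes | yes | yes | yes | yes | no | yes | no |

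**3. Reading the table.**
- The first two rows are ordinary TN. As written, they have no route under either parse.
- As written, the only type that criterion 4 adds to criteria 1 and 3 is metaplastic, not high grade, not inflammatory (row 5). That is an unlikely purpose for a criterion placed last among the TN groups.
- With the corrected wording, both ordinary-TN rows enter through criterion 4, and criterion 4 overlaps with neither criterion 1 nor criterion 3.
- Row 5 then loses its only route. The correction therefore does not cover every TN tumour.

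**4. Against the introductory sentence.** It names TN cancer in the neoadjuvant setting and sets no histological limit. Criterion 4 as written removes ordinary TN from exactly that setting. No other section corrects or explains the wording.

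**5. Sample size, as context only.** The plan's pooled rate is 2/3 × 10% + 1/3 × 30% = 16.7%, which it rounds to 17%. With a Wald interval, the lower bound is 0.17 − 1.96 × √(0.17 × 0.83 / 65) = 0.079, and 65 × 0.079 ≈ 5.1. The plan rounds the bound to 8% and gets 5.2. The total of 85 is 65 × 1.30 = 84.5, rounded up. None of these figures uses the wording of criterion 4.

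The document gives no histology mix, so any loss of TN patients has to be assumed. The figures below are illustrations only. They hold 65 tumours fixed and replace the missing TN tumours with luminal B:

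| TN share (assumed, except 1/3) | Pooled rate | 65 × Wald lower bound | P(at least 5 successes in 65) |
|---|---|---|---|
| 1/3 (plan) | 16.7% | 4.9 | 0.99 |
| 20% | 14% | 3.6 | 0.96 |
| 10% | 12% | 2.7 | 0.90 |

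**The case against.** The strongest reply is that the meaning can be recovered. The list runs metaplastic, inflammatory, then a residual group, and the introductory sentence points the same way. The trial is single-centre, so few people have to share that understanding. The text is also a journal article: Trial status names an approved protocol (version 02) that is not shown, and the slip may be confined to the article. All of this stands. It limits how much harm is likely, but it does not make the published criterion right, and it is the reason for checking the approved text.

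It can also be said that the introductory sentence is only a summary. That is fair: it is also broader than the table for primary surgery, where only high grade metaplastic TN is admitted. The sentence alone would be thin evidence. Together with the order of the list and the near-emptiness of criterion 4 as written, it is enough.

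A reader might go further and infer that high grade metaplastic tumours face two conflicting size limits. They do not. The criteria are joined by OR, so such a tumour qualifies at 15 mm under criterion 1, and the 30 mm in criterion 4 is redundant for it. A reader might also infer that ordinary TN is shut out of the trial altogether. It is not: with an operable metastasis it remains eligible under criterion 6.

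**Conclusion.** The point holds as a wording error in an eligibility criterion. Under either parse, non-metaplastic, non-inflammatory TN after neoadjuvant chemotherapy has no non-metastatic route into the trial, contrary to the introduction to the table and the evident order of the list. This rests on the article's text alone; whether the approved protocol carries the same words is unknown.

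The effect on the TN share and on the pooled success rate cannot be quantified from the document. TN carries 10 of the 16.7 percentage points of the expected rate (1/3 × 30%), so it is tempting to conclude that the wording endangers the target of five successful grafts. The document does not support that. The shares of 20% and 10% are assumptions. The plan states its mix as intended, so if that mix were held, fewer eligible TN patients would slow accrual and not lower the rate. Even with substitution by luminal B, the chance of five or more successes stays at 0.96 or 0.90. The lower-bound count does fall below five, but that is the device used to choose the sample size; the feasibility rule is the number of successes observed. No sample-size figure needs to change.

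**What to change.** Reword criterion 4 so that it describes the residual group, for example *TN breast cancer other than metaplastic or inflammatory (T4d)*, and reconcile it with criteria 1 and 3 and with the introductory sentence. Leave the size thresholds as they stand.

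Two checks go with it:
- Compare the wording in the approved protocol and on the eligibility form. If it is the same there, correct it there too, and establish which reading was applied to any patient already screened.
- Have the sponsor state whether metaplastic TN that is not high grade is meant to be excluded. It has a route only under the present wording and would have none in the non-metastatic setting after the correction.

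The cost is a one-line text change plus the document check. Sample size and analysis are unaffected.

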### Recruitment and consent

Eligible patients will be offered the opportunity to participate in the study by their oncologist or their surgeon. Patients who agree to participate in this study will provide written informed consents (clinical consent and genetic consent) for enrolment. XenTech is allowed to commercialize the PDX generated in this project. The patients will be made aware of that during consent.

### Sample size calculation

This feasibility study aims to obtain xenografts from tumours that are either rare or tumours that are resistant to treatment and therefore difficult to establish. We consider that a minimum of five successful grafts would meet this objective. Under these conditions, knowing the graft success rate specific to each histological type and the proportion of luminal B (2/3) and triple-negative breast cancers (1/3), we calculate the number of subjects required so that the lower bound of the 95% confidence interval (CI) of the success rate multiplied by the number of subjects is ≥5.

To obtain a xenograft, the average rate is 30% from triple-negative tumours and 10% from luminal B tumours. Taking these data into account, we will include 2/3 luminal B tumours and 1/3 triple negative tumours: the expected rate of successful xenografts will be approximately 17%. The number of patients needed to be included is therefore at least 65: lower bound of the CI-95% of 17% for 65 subjects = 8% or 5 patients (8%×65=5.2).

Since for some patients the tumour will be of sufficient size for imaging, but of insufficient size in the operating room, we consider that this number should be increased by 30%, to a total number of 85 patients.

### Study objectives and data collections

The primary objective of the XENOBREAST trial is to establish xenografts from tumour samples of patients with triple negative or luminal B breast cancer in neoadjuvant, adjuvant or metastatic setting. Furthermore, the study aims to investigate histomolecular characteristics of the established PDX and to compare these characteristics with the initial histomolecular profile of the collected tumours.

Data collected are the patient's age (month and year of birth), pathology, treatments received, response to treatments, date and nature of surgery (primary tumour, metastasis), data concerning exomes (constitutional and tumour), as well as histomolecular profiles of the initial tumour and of the different xenograft generations. To define these histomolecular profiles we will quantify the expression of the oestrogen, progesterone and androgen receptors by immunohistochemistry, the amplification status of the
*ERBB2* gene, and the fraction of tumour cells expressing Ki67. Finally, tumours will be classified into molecular classes according to the above-mentioned data: luminal A, luminal B, HER2-enriched or triple negative.

Data collected and transmitted to the sponsor of the study by the investigators will be pseudonymized. Study data will not contain any names or other personal identifiers such as addresses. Patients included in the trial will be identified by a code specific to this trial. The investigator will have access to the correspondence table between the patient's last name, first name, date of birth and the code assigned in the trial.

